5.7 Emergency treatment

During and after the clinical trial, the investigator must ensure that, in the case of UEs, the trial subjects always receive adequate medical care.

**6. DESCRIPTION OF THE STUDY VISITS**

For the individual patient, the duration of the study consists of an intervention (PTBD or EUCD) followed by an observation period of 6 months. Before the treatment phase, there is a screening phase with examination of the inclusion and exclusion criteria.

Overview of the study visits and the data to be collected (Fig 1)

[figure not shown]

6.1 Screening visit

A paper-bound explanation of the study (own form) for the intervention (commercial form) and the sedation or anaesthesia (commercial form) of the patient is provided. Each potential study patient will receive a CT or MRI abdomen in addition to an abdominal sonography. The inclusion and exclusion criteria are checked (Case Report Form , p.2). Every patient who has been positively screened is included in the study if written consent is obtained (Case Report Form, p. 1). In the case of patients who are still capable of giving birth, a possible pregnancy is excluded by pregnancy tests.

It is assumed that almost all positively "screened" patients want to undergo an intervention under study conditions. In this situation, surgery is usually either not possible (pre-operated abdomen, advanced tumour disease) or is associated with a considerable risk. The performance of a PTBD/EUCD is therefore mostly without alternative. The screening list lists (separate form) which patients have been screened positively (inclusion and exclusion criteria fulfilled). Should a patient not be included in the study (e.g. because of refusal to participate in the study), this is briefly explained.

6.2 Baseline visit

Facts of the clinical picture are documented (Case Report Form,p.3) . Cause of malignant bile duct obstruction, date of first diagnosis of the malignant underlying disease, cause of unsuccessful or for anatomical reasons not feasible ERCP.

The bilirubin value in mg/dl as an expression of the bile duct obstruction or cholestasis is measured and noted. The baseline visit should be performed the day before the intervention. Depending on the timing within the centre, baseline visit can be on the same day as screening visit if the intervention is scheduled for the following day.

Data that are documented as part of the study:

Demographics

- Gender

- Age

- Size

- Weight

Cause of the malignant bile duct obstruction (no multiple answers)

- Pancreatic carcinoma

- Distal bile duct carcinoma or extrahepatic bile duct carcinoma (Bismuth I)

- Gall bladder carcinoma

- Stomach cancer

- Duodenal carcinoma

- Papillary carcinoma

- Metastasis of another malign disease

- Other cause

Date of first diagnosis of the underlying malignant disease

Cause of unsuccessful or for anatomical reasons not feasible ERCP (no multiple answers)

- Gastric outlet stenosis/duodenal stenosis (tumour-related or benign cause)

- Difficult to probe the optic disc using ERCP

- For (partial) gastrectomy

- Biliodigestive anastomosis

- Following bariatric surgery

- Other cause

Laboratory chemical result of bilirubin determination (in g/dl) Pain intensity on the visual analogue scale (0-10)

6.3 Treatment rounds (intervention day)

Characterisation of the respective intervention: PTBD or EUCD (Case Report Form, p.4). The duration of the intervention is noted in minutes, the technical success with "yes/no". Adverse events (description, classification into light, medium, severe and fatal) are documented.

Data documented within the study:

Date of the intervention Start of the intervention

PTBD: Start with skin anaesthesia

EUCD: Start of endoscope insertion End of intervention PTBD: Completion of skin dressing EUCD: Removal of endoscope from patient Dimensions of metal stent

Wrapping of the metal stent Intervention technically successful

PTBD/EUCD: Contrast medium outflow via the metal stent (max. 1min. after injection)

PTBD Localization

PTBD with metal stent implantation

Number of PTBDs before metal stent implantation

PTBD with metal stent release under endoscopic control

EUS-controlled, antegrade drainage (EUS-AD)

EUS-guided transhepatic drainage (EUS-HD)

EUS-guided choledochal drainage (EUS-CD)

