**2. OBJECTIVES AND ENDPOINTS**

Primary objective and primary endpoint

The primary objective of the study is to show that PTBD is not inferior to EUCD in terms of technical success rate. The technical success rate is defined as the successful implantation of a metal stent into the bile duct system (= successful drainage of the contrast medium via the metal stent within one minute after injection).

The primarily technical success of the intervention is decisive for the further procedure following the examination (reintervention necessary ? surgery necessary ?) and is presumably almost identical to the clinical success of the intervention, which can only be verified after 7 days (drop in bilirubin value ≥ 50%). The technical success rate was therefore preferred to the clinical success rate as the primary endpoint.

In PTBD there is only one possibility of metal stenosis insertion across the tumor stenosis in the common bile duct (blunt). In EUCD, the additional option of transluminal stent placement in the context of EUS-HGS or EUS-CDS remains.

The prompt (1 week) implantation of a metal stent after the application of an external drainage in PTBD is also considered a technical success. However, the application of an external drainage is counted as "reinvention".

Secondary objectives and secondary endpoints

In addition to the technical success rate, both interventions will be compared descriptively with regard to other endpoints. All endpoints or points in time refer to the technically successful intervention.

1. Clinical success rate of bile extraction, defined as reduction of the bilirubin value of ≥ 50% 7 days after technically successful intervention in relation to the baseline value before intervention.

2. The occurrence of at least one complication (including death) within 30 days (description + count)

3. Duration of bile duct intervention (PTBD/EUCD) in minutes

- for PTBD: from the application of the local anaesthetic to the application of the skin dressing

- for the EUCD: from the insertion of the endoscope to the removal of the endoscope

4. Post-interventional pain sensation on day 1 and day 7 after intervention (in relation to baseline before intervention): visual analogue scale

5. Length of hospital stay (from the day of the first intervention to the day of discharge) in days

6. Number of re-interventions between the first intervention and the end of the follow-up

(n) after 6 months.

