5.5 Re-interventions

Re-interventions are defined as renewed or repeated performance of PTBD or EUCD. Re-interventions may become necessary to complete a technically successful implantation of a metal stent in the bile duct. This may be the case, for example, if in the case of PTBD only the creation of an external drainage (drainage to the outside, no overcoming of the tumor stenosis) was possible in the first intervention. Planned re-interventions are avoided within the study concept (e.g. leaving the external/internal drainage after technically successful PTBD with stent implantation and radiological control of the result on the following day). After technically successful implantation of the metal stent, stent closure, stent migration (change of position) or other stent malfunction may occur in the further course (following months). This is usually clinically visible by an increase in the laboratory chemical parameters for bile duct occlusion (increase in bilirubin, increase in alkaline phosphatase) or by cholangitis (additional signs of infection). Any Re-intervention on the bile duct that is related to the primary method used, PTBD or EUCD, is considered as re-intervention in the documentation of the data. Thus, an operation (for example: creation of a biliodigestive anastomosis) which becomes necessary as a result of the "malfunction" of the metal stent is also counted as a re-intervention (!).

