6.4 Control visits

On the day after the technically successful intervention, the patient's pain sensation is recorded by means of a visual analogue scale (0-10) (Case Report Form; Control Visit No.1, p.5).

The next visit is on day 7 after the technically successful intervention (Case Report Form; Control Visit No.2, p.6). If a re-intervention is necessary (see Chapter 2.1), the count is only made from the day of successful intervention (metal stent implantation). If the patient is discharged from the hospital within the seven days after technically successful intervention, it must be ensured that the attending general practitioner carries out the laboratory check and the result is obtained from the general practitioner. The determination of bilirubin has been so standardized for many years that no central laboratory is necessary. In addition, the intensity of pain according to the visual analogue scale (0-10) must be obtained from the investigating physician or his representative by telephone or post on day 7 after a technically successful intervention. Adverse events and re-interventions, including the patient's discharge day (which is counted), are documented to determine the length of hospital stay in days.

The patient is called to a staging by means of CT or MRI abdomen after three (no data collection here) and six months of the technically successful intervention as an outpatient or inpatient (not study related). The date six months after intervention should be used for a detailed study visit. Previously undocumented complications in a 30-day interval and reinterventions within the six months after the intervention will be documented (Case Report Form; Control Visit No. 3, pp.7-8). If the patient is not examined at the trial centre, it must be ensured that the relevant data on re-interventions or complications can be obtained by calling the family doctor or patient.

If the patient should be referred to tumor therapy (palliative chemotherapy, immunotherapy, antibody therapy) as part of the malignant underlying disease, this will be documented with "yes/no" and the therapy will be named. It can be assumed that a tumor therapy has a positive influence on the re-intervention rate as well as on the disease-specific survival and overall survival.

Data documented in the study

Control visit no.1 (1 day after intervention)

Intensity of pain on the visual analogue scale (0-10) Complication(s) since intervention (yes/no)

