Serious adverse events (SUE) since intervention (yes/no)

Control visit no.2 (7 days after technically successful intervention

Intensity of pain on the visual analogue scale (0-10) Date Bilirubin determination (after initial intervention)

Laboratory chemical result of the bilirubin determination (after initial intervention, in mg/dl)

Duration of hospital stay from day of intervention (inclusive) to day of discharge (date of hospital discharge, if later than 7 days, please add later!)

Re-intervention(s) since control visit 1 (yes/no) Complication(s) since control visit 1 (yes/no)

Serious adverse events (SUE) since intervention (yes/no)

Control visit no.3 (6 months after intervention) and/or study completion visit

The final study visit coincides with the follow-up visit after six months. To calculate the Overall Survival or Disease Specific Survival, it is noted whether the patient is still alive or when he/she died and why (date of death, calculation of survival time in days, cause of death). If the patient is not examined at the trial centre or has died in the meantime, it must be ensured that the relevant data on re-intervention, adverse events, date of death and cause of death can be obtained by calling the family doctor or relatives.

Data that are documented within the framework of the study:

Date of end of study/last contact

Reason for termination:

- Regular termination of the study (yes/no)

- Patient has died (yes/no)

Date of death

Cause of death on the ground of the underlying malignant disease (yes/no)

Cause of death other than underlying malignant disease (yes/no)

Cause of death unclear (yes/no)

Revocation of consent (yes/no)

Patient no longer appeared/follow-up data no longer to be collected (yes/no)

Intervention not successful, no new attempt

Other (specification)

Chemotherapy carried out during the course (yes/no)

Chemotherapy protocol (name): first line/second line/third line (multiple answers possible)

- Gemcitabine mono (yes/no)

- Gemcitabine/Nab-paclitaxel (yes/no)

- FOLFIRINOX (yes/no)

- Cisplatin/Gemcitabine (yes/no)

- FLO (T) (yes/no)

- FOLFIRI (yes/no)

- Paclitaxel/Ramucirumab (yes/no)

- Ramucirumab mono (yes/no)

- 5 FU mono (yes/no)

- Other chemotherapy/immunotherapy (yes/no)

Other therapy (but no chemotherapy) performed (yes/no)

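### The intervention-day list counts sessions before stent success for PTBD only, so EUCD repeats before success may be missing from the re-intervention endpoint

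*Protocol*

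**What the plan says.** **Endpoint.** Protocol Section 2, secondary endpoint 6, is the "Number of re-interventions between the first intervention and the end of the follow-up" at six months. Section 5.5 states that "Re-interventions are defined as renewed or repeated performance of PTBD or EUCD", and adds that repeats may be needed to complete a successful stent placement. Section 2 also counts an external drainage in PTBD as a re-intervention when the stent follows within a week.

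**Intervention day (Section 6.3).** For PTBD the list includes "Number of PTBDs before metal stent implantation". For EUCD it names the technique only, for example "EUS-guided transhepatic drainage (EUS-HD"), with no count of attempts.

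**Control visits (Section 6.4).**
- Visit 1: "On the day after the technically successful intervention, the patient's pain sensation is recorded". The other listed items are complications ("Complication(s) since intervention (yes/no") and serious adverse events. There is no re-intervention item.
- Visit 2: "Re-intervention(s) since control visit 1 (yes/no").
- Visit 3: the text says that "reinterventions within the six months after the intervention will be documented (Case Report Form; Control Visit No. 3, pp.7-8"). The item list for visit 3 contains no re-intervention entry, although the paragraph that introduces it mentions obtaining such data by telephone.

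**The concern.** The endpoint is a number with the same starting point in both arms, but the listed fields give that number an early component in one arm only. A PTBD patient who needs a second session before the stent is placed has that session counted on the intervention-day list. An EUCD patient in the same position has no matching item, and the failed session lies before visit 1, so the visit 2 item does not reach it.

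This bears on a question that the study sets itself. Section 1.3 says the study should show how far the higher re-intervention rate attributed to PTBD really applies, and Table 1 in Section 1.1 criticises how some earlier comparisons counted re-interventions. If early sessions are collected for PTBD and lost for EUCD, the excess under examination would arise partly from data capture.

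**Working it through.** **Step 1. Which records can hold a re-intervention, by time and arm.**

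| When it happens | PTBD | EUCD |
| --- | --- | --- |
| Before stent success | Counted in the Section 6.3 list | No item in 6.3; visit 3 only if its window starts at the first session |
| After success, before visit 1 | Visit 3 record | Visit 3 record |
| Visit 1 to visit 2 | Visit 2 (yes/no) and visit 3 record | Same |
| Visit 2 to month 6 | Visit 3 record | Same |

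Only the first row differs between the arms.

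**Step 2. Does the visit 3 record close the gap in the first row?** It covers six months after the intervention, without saying which one. Section 2 ties all secondary endpoints and time points to the technically successful session, and Section 6.4 times the visits from that session; on that reading, earlier sessions fall outside. Yet endpoint 6 starts at the first intervention, and the visit 3 sentence omits the qualifier that Section 6.4 uses elsewhere; on that reading, they fall inside. The text does not settle it.

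**Step 3. Does the asymmetry reach the endpoint?** This depends on the counting rule.
- If counting starts at the first intervention, as endpoint 6 and Section 5.5 say, sessions before success belong in the number, and a loss in EUCD alone makes PTBD look worse.
- If only re-interventions after success count, as the general sentence in Section 2 could suggest, sessions before success drop out of both arms. The PTBD field is then unused and there is no directional bias.

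The more specific text supports the first rule.

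**Step 4. Form of the data.** A yes/no answer at visit 2 cannot supply a number. If the visit 3 record does not give number and dates, two re-interventions between visits 1 and 2 cannot be told from one. This affects both arms alike.

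**Step 5. Size.** Planned arm size (Section 9.1): 100 / (1 − 0.05) = 105.3, rounded up to 106, as stated. Let r be the mean number of repeat EUCD sessions per patient before success, and c the share of these captured elsewhere. The undercount per patient is r × (1 − c). The protocol gives neither r nor c. As an illustration only, assume r = 0.05 to 0.10:
- c = 0: 0.05 to 0.10 per patient, or 106 × 0.05 = 5.3 to 106 × 0.10 = 10.6 sessions in the arm;
- c = 1: none.

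Each single missed session lowers the EUCD mean by 1/106 = 0.009.

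**The case against.** The strongest reply is that the Chapter 6 lists are not the case report form, which is not shown, and are visibly incomplete. Section 6.3 requires adverse events in its text but lists no such item, and the visit 3 list omits the 30-day complications that the text places on the same form pages. Section 10.1 requires the forms to capture everything the protocol asks for, Section 5.5 says any related re-intervention is counted in the documentation, and the day-7 paragraph of Section 6.4 also mentions documenting re-interventions. The intervention page records date, start, end and success for either method; if it is completed once per session, repeat EUCD attempts are recorded. A PTBD-specific field also has a rationale, since Section 2 describes staged stenting for PTBD only.

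Much of this stands: it cannot be said that EUCD repeats are certainly lost. It does not remove the point. Section 7 refers to Chapter 6 for what is collected, and Section 10.1 has the forms built from the protocol, so an asymmetry in the lists is likely to carry over. Nothing says that the intervention page is repeated per session, and a separate count of earlier PTBDs would be largely redundant if it were.

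Three stronger readings are tempting but not supported:
- A reader might infer that re-interventions in the first day after success are never recorded. The six-month record covers them, late and in retrospect, and equally in both arms.
- A reader might infer bias against PTBD under any counting rule. It disappears if only re-interventions after success count.
- A reader might express the loss as a percentage of the EUCD total. That needs an assumed repeat rate, an assumed mean and no capture elsewhere; the documents give none of these.

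**Conclusion.** The point holds in limited form. The only listed count of sessions before success is for PTBD, and the one record that might cover EUCD has an unclear start and is missing from its own item list. EUCD repeats before success may therefore be undercounted relative to PTBD.

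The direction, against PTBD, rests on two assumptions: that sessions before success count, as endpoint 6 and Section 5.5 indicate, and that neither the intervention page nor the visit 3 record captures them in EUCD. The size cannot be derived from the documents.

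The consequence is bounded. Under Section 9.2 re-interventions lie outside the hierarchical test and are analysed descriptively, so the primary non-inferiority conclusion is unaffected. The correction is still worthwhile because the comparison is part of the study's rationale and an analysis plan cannot recover sessions that were never recorded.

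**What to change.** 1. In Section 6.3, replace the PTBD-only item with one for both arms: the number of PTBD or EUCD sessions before the metal stent was placed, with the date of each.
2. In Section 6.4, record re-interventions at visit 2 as number and dates instead of yes/no, and add the same entry to the visit 3 item list.
3. State in Section 6.4 that the re-intervention record runs from the first intervention in both arms, and align the general sentence in Section 2 on time points with endpoint 6.

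The cost is a few form fields and matching protocol wording, with no extra visit or procedure.

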6.4 Control visits

On the day after the technically successful intervention, the patient's pain sensation is recorded by means of a visual analogue scale (0-10) (Case Report Form; Control Visit No.1, p.5).

The next visit is on day 7 after the technically successful intervention (Case Report Form; Control Visit No.2, p.6). If a re-intervention is necessary (see Chapter 2.1), the count is only made from the day of successful intervention (metal stent implantation). If the patient is discharged from the hospital within the seven days after technically successful intervention, it must be ensured that the attending general practitioner carries out the laboratory check and the result is obtained from the general practitioner. The determination of bilirubin has been so standardized for many years that no central laboratory is necessary. In addition, the intensity of pain according to the visual analogue scale (0-10) must be obtained from the investigating physician or his representative by telephone or post on day 7 after a technically successful intervention. Adverse events and re-interventions, including the patient's discharge day (which is counted), are documented to determine the length of hospital stay in days.

The patient is called to a staging by means of CT or MRI abdomen after three (no data collection here) and six months of the technically successful intervention as an outpatient or inpatient (not study related). The date six months after intervention should be used for a detailed study visit. Previously undocumented complications in a 30-day interval and reinterventions within the six months after the intervention will be documented (Case Report Form; Control Visit No. 3, pp.7-8). If the patient is not examined at the trial centre, it must be ensured that the relevant data on re-interventions or complications can be obtained by calling the family doctor or patient.

If the patient should be referred to tumor therapy (palliative chemotherapy, immunotherapy, antibody therapy) as part of the malignant underlying disease, this will be documented with "yes/no" and the therapy will be named. It can be assumed that a tumor therapy has a positive influence on the re-intervention rate as well as on the disease-specific survival and overall survival.

Data documented in the study

Control visit no.1 (1 day after intervention)

Intensity of pain on the visual analogue scale (0-10) Complication(s) since intervention (yes/no)

Serious adverse events (SUE) since intervention (yes/no)

Control visit no.2 (7 days after technically successful intervention

Intensity of pain on the visual analogue scale (0-10) Date Bilirubin determination (after initial intervention)

Laboratory chemical result of the bilirubin determination (after initial intervention, in mg/dl)

Duration of hospital stay from day of intervention (inclusive) to day of discharge (date of hospital discharge, if later than 7 days, please add later!)

Re-intervention(s) since control visit 1 (yes/no) Complication(s) since control visit 1 (yes/no)

Serious adverse events (SUE) since intervention (yes/no)

Control visit no.3 (6 months after intervention) and/or study completion visit

The final study visit coincides with the follow-up visit after six months. To calculate the Overall Survival or Disease Specific Survival, it is noted whether the patient is still alive or when he/she died and why (date of death, calculation of survival time in days, cause of death). If the patient is not examined at the trial centre or has died in the meantime, it must be ensured that the relevant data on re-intervention, adverse events, date of death and cause of death can be obtained by calling the family doctor or relatives.

Data that are documented within the framework of the study:

Date of end of study/last contact

Reason for termination:

- Regular termination of the study (yes/no)

- Patient has died (yes/no)

Date of death

Cause of death on the ground of the underlying malignant disease (yes/no)

Cause of death other than underlying malignant disease (yes/no)

Cause of death unclear (yes/no)

Revocation of consent (yes/no)

Patient no longer appeared/follow-up data no longer to be collected (yes/no)

Intervention not successful, no new attempt

Other (specification)

Chemotherapy carried out during the course (yes/no)

Chemotherapy protocol (name): first line/second line/third line (multiple answers possible)

- Gemcitabine mono (yes/no)

- Gemcitabine/Nab-paclitaxel (yes/no)

- FOLFIRINOX (yes/no)

- Cisplatin/Gemcitabine (yes/no)

- FLO (T) (yes/no)

- FOLFIRI (yes/no)

- Paclitaxel/Ramucirumab (yes/no)

- Ramucirumab mono (yes/no)

- 5 FU mono (yes/no)

- Other chemotherapy/immunotherapy (yes/no)

Other therapy (but no chemotherapy) performed (yes/no)

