**5. TREATMENTS/ INTERVENTIONS**

5.1 Description of the treatment(s)/ intervention(s)

PTBD

PTBD is performed in the first step by means of (colour contrast Doppler) ultrasound-guided puncture of an (dilated) intrahepatic bile duct using an access needle (e.g. Chiba needle (22G/0.7mm diameter). In the next step, the application of contrast medium into the bile duct system is performed under radiological fluoroscopy. The access route should be at a sufficient safety distance from neighbouring structures, i.e. the pleura in case of right-sided access.

Ideally, after KM filling of the bile duct system, a wire should be advanced distally beyond the stenosis in the common bile duct. This can also be done after changing to a larger wire (from 0.018" to 0.035"). After placement of an appropriate guide wire, a corresponding metal stenosis implantation (SEMS) should be performed in the same session in the area of the stenosis of the common bile duct (usually 8 or 10 mm diameter with different lengths (usually 6 -10 cm).

For further precision, the release of the metal stent can (not obligatory) be controlled by an additional luminal endoscopic visualization. (usually in relation to the papilla or the protrusion into the duodenum). This is particularly relevant with regard to endoscopic reintervention. Even in cases of tumour-related duodenal stenosis (use of a thinner endoscope) or altered anatomy after abdominal surgery (e.g. access via the feeding loop after Billroth II surgery). it is very often possible to reach the papilla (e.g. using a gastroscope).

Leaving a percutaneous plastic drainage after successful implantation of a metal stent should be avoided (counted as reintervention). If metal stent implantation is not possible in the initial PTBD, an internal/external plastic drainage should be inserted and the sole external drainage should be avoided (highest risk of complications).

EUCD

Endosonographically controlled cholangiodrainage (EUCD) is performed according to the current state of knowledge of this technique (2-9,14,15).

The choice of the respective EUCD method depends on the examiner. First and foremost, however, an antegrade stenting in the sense of an EUS-AD (wire is passed over the stenosis) should be performed.

should be attempted, since - in contrast to the transluminal procedure - the original anatomy of the bile duct system is preserved and the least complications are expected.

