The evaluation of further secondary endpoints is done in the ITT set. With regard to the complication rate, PTCD is expected to have a lower complication rate than EUCD. No missing values are implanted during the evaluation of secondary endpoints. The evaluation is purely descriptive. Appropriate statistical methods are used according to the underlying distribution. For continuous endpoints, the mean, standard deviation, median, interquartile distance, and minimum and maximum are reported separately and in total for the two groups. For categorical endpoints, absolute and relative frequencies are given, also separately for the two groups and in total. Event times are displayed and evaluated using survival time analysis methods (e.g. Kaplan Meier). Descriptive p-values are given together with 95% confidence intervals. In the EUCD group, descriptive p-values are also divided by method (see 5.1). In addition, unless defined in the secondary endpoints, adverse events are evaluated and compared.

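### The clinical success clock starts at the metal stent but the reference bilirubin predates the first session, so staged PTBD patients can have up to 14 days of drainage against 7, and the visit 2 data item contradicts that clock

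*Protocol*

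**What the plan says.** **Definition.** Protocol section 2, secondary endpoint 1, defines clinical success as "reduction of the bilirubin value of ≥ 50% 7 days after technically successful intervention in relation to the baseline value before intervention". The general rule above the list is "All endpoints or points in time refer to the technically successful intervention". Section 7.2.2 gives the same threshold, counted from the completed intervention.

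**Clock after a re-intervention.** Section 6.4: "the count is only made from the day of successful intervention (metal stent implantation".

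**Reference value.** Section 6.2 lists one baseline bilirubin: "The baseline visit should be performed the day before the intervention". No further value is listed before a stent placed at a later session.

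**Staging.** Section 2: "The prompt (1 week) implantation of a metal stent after the application of an external drainage in PTBD is also considered a technical success". Section 5.1 describes what is left in place meanwhile: "If metal stent implantation is not possible in the initial PTBD, an internal/external plastic drainage should be inserted". No corresponding interim drain or one-week allowance is described for EUCD.

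**Data item.** Control visit no. 2 in section 6.4 is headed as 7 days after the technically successful procedure. Its bilirubin item nevertheless reads "Laboratory chemical result of the bilirubin determination (after initial intervention, in mg/dl", and the item for the date of that measurement carries the same label.

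**The concern.** Bilirubin begins to fall once bile drains, whether through a temporary drain or a metal stent. Under the definition as written, a staged PTBD patient enters the 7-day count with some fall already achieved, yet that fall is measured from the value before the first session. The endpoint then credits the stent with part of the temporary drain's effect. Because only PTBD has both a described interim drain and a staging allowance, the extra time goes to one arm.

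The contradictory data item adds a second problem. In a staged patient, seven days after the first session and seven days after the stent are different dates. Sites can reasonably enter either, and the analysed rate would then mix two definitions.

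At stake is how the clinical success rates are read. Section 2 supports technical success as primary endpoint partly by expecting it to agree closely with clinical success, and section 1.2 wants the success rates to inform which method should be preferred after failed ERCP.

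**Working it through.** **The plan's own figures.** The protocol gives no planned rate or sample size for clinical success. Its one sample size concerns technical success: 95% in both arms, margin 0.10, one-sided 2.5%, 80% power. The Farrington-Manning formula gives n = 99.4, so 100 per group, and 100 / 0.95 = 105.3, so 106. Both agree with section 9.1 and neither depends on the clinical success definition.

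**Drainage time at the reading.**
- Time at the reading = gap from first drainage to stent + 7 days (sections 2 and 6.4).
- Stent in the first session: 0 + 7 = 7 days.
- Staged PTBD at the longest gap allowed in section 2: 7 + 7 = 14 days.
- EUCD repeated after a failed first attempt: the clock also restarts, but with no interim drain described, drainage at the reading is still 7 days.

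**What the extra time means.** A 50% fall in 7 days needs a mean decline of 1 − 0.5^(1/7) = 9.4% per day. In 14 days it needs 1 − 0.5^(1/14) = 4.8% per day.

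**Illustrative size.** The protocol gives no bilirubin kinetics, staged share or typical gap, so all three are assumptions. Let the half-life under drainage be log-normal with median m and log-SD 0.5. A patient succeeds if the half-life does not exceed the drainage time t, so P(success) = Φ(ln(t/m)/0.5).

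| Median m | t = 7 days | t = 10 days | t = 14 days |
|---|---|---|---|
| 5 days | 0.750 | 0.917 | 0.980 |
| 7 days | 0.500 | 0.762 | 0.917 |

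The rise in the PTBD rate with no better drainage is staged share × [P(t) − P(7)].

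Full 7-day gap (t = 14):
- m = 5: 0.980 − 0.750 = 0.230. At 10% staged, 2.3 points; at 25%, 5.8 points.
- m = 7: 0.917 − 0.500 = 0.417. At 10% staged, 4.2 points; at 25%, 10.4 points.

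3-day gap (t = 10):
- m = 5: 0.917 − 0.750 = 0.167. At 10% staged, 1.7 points; at 25%, 4.2 points.
- m = 7: 0.762 − 0.500 = 0.262. At 10% staged, 2.6 points; at 25%, 6.6 points.

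**The contradiction needs no assumption.** Sections 2, 7.2.2 and the text of 6.4, together with the visit 2 heading, point to the successful or completed procedure. The two visit 2 bilirubin labels point to the initial one. The dates coincide when the stent is placed in the first session and differ by the length of the gap in a staged patient. Followed literally, the label would remove the extra time; the definition would keep it.

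**The case against.** **The anchor is deliberate.** Section 2 ties the endpoints to the technically successful procedure, and 6.4 and 7.2.2 follow. This stands as a reason to keep a stent-anchored rate. Seven days after the first session, a patient stented on day 7 shows mainly or only the temporary drain's effect. Choosing between the anchors is a judgement about what to estimate. It does not make the drainage times equal.

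**Staging should be uncommon.** The protocol wants the stent in the first session whenever possible and avoids planned re-interventions. This also stands: 14 days is a maximum, applies only to staged patients, and high staged shares run against the intended technique. Staging is still foreseen. The literature table in section 1.1 records 4 external drainages before stenting among 12 PTBDs in one prospective study, and section 6.3 collects how many PTBDs preceded the stent.

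**The endpoint is descriptive.** Correct: it lies outside the hierarchical test.

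**Staged patients can be identified from the data.** The intervention date, the number of earlier PTBDs and the bilirubin date are all collected. That allows separate reporting, but no analysis can supply a bilirubin value on a date when none was taken.

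**A stronger reading about deaths.** A reader might infer from "No missing values are implanted during the evaluation of secondary endpoints" in section 9.2 that patients who die before day 7 are dropped from clinical success. The document does not say so. Secondary endpoints use the ITT set, and counting a death as failure classifies an outcome; it does not impute one. The protocol leaves these patients unclassified for this endpoint, and the SAP may settle it. Nothing in the protocol shows early death differing by arm.

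**Conclusion.** The point holds for the unequal drainage window and for the contradictory data item. As defined, clinical success can be read after up to 14 days of drainage in staged PTBD patients and after 7 days in patients stented at the first session, which favours PTBD. Under the assumed half-lives, the maximum gap is worth about 2 to 4 points on the PTBD rate at 10% staged and 6 to 10 points at 25%, and less with shorter gaps. These are illustrations: the half-life, the staged share and the gap are not protocol figures.

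The effect is confined to a descriptive secondary endpoint. It does not touch the non-inferiority test, the hierarchical complication test or the sample size. It also does not extend to all PTBD patients: those stented in one session are on the same window as EUCD. The change is worth making because it is cheap and the bias has a known direction.

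**What to change.** 1. Reconcile the two visit 2 bilirubin labels in section 6.4 with the visit heading, the 6.4 text and sections 2 and 7.2.2, so that each bilirubin value has one defined date.
2. For staged patients, record bilirubin both 7 days after the first drainage session and 7 days after stent placement, each against the value before the first session.
3. Compare the arms on the common window from first drainage. Report the stent-anchored rate beside it, and show staged PTBD patients separately.

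The cost is wording in sections 2, 6.4 and 7.2.2, a changed CRF label with a second field, and possibly one extra routine bilirubin value in staged patients. The drawback is that the first-drainage value may partly or wholly reflect the temporary drain instead of the stent, which is why both rates should be reported. No treatment changes.
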